## Abstract

This study proposes the validation of the Virtual Spatial Configuration Task (VSCT), a novel task designed to evaluate cognitive map formation abilities in participants. Addressing a notable gap in spatial cognition research, particularly in the assessment of higher-level spatial abilities in 3D environments, the VSCT offers a virtual reality (VR) approach that allows users to explore and recall spatial relationships between landmarks. This task is particularly innovative for populations with impaired mobility, as it simplifies navigation by restricting movement to rotational exploration, thus improving accessibility and reducing motion sickness. Furthermore, the VSCT could serve a dual purpose: assessing spatial orientation skills while also providing a platform for training and improving these skills post-injury. The potential applications of this tool extend to neurorehabilitation and other therapeutic interventions, offering an engaging, immersive method for enhancing spatial abilities.

## Introduction

“Spatial ability can be defined as the capacity to generate, retain, retrieve and transform spatial representations” (
Burles, 2014 pp.4). Those abilities depend on multiple sensory cues, computational mechanisms, and spatial representations (
[name], 2021). The efficacy of spatial orientation and navigation depends on the complex integration and manipulation of multisensory information across time and space. Spatial abilities in humans have been investigated using two types of tasks: figural-scale and environmental-scale (
Jansen, 2009). Figural-scale tasks assess abilities such as spatial perception, mental rotation, visualization, and orientation (
Linn & Petersen, 1985), and environmental-scale tasks involve large stimuli like rooms, buildings, and neighborhoods (
Hegarty *et al*., 2006).

As pointed out by
Bartlett and Camba (2022), spatial ability tests that attempt to assess 3D abilities through 2D media have limitations: Any 2D image is inherently ambiguous when it comes to interpreting a 3D shape from the image (
Pizlo, 2008). Black and white line drawings used in these tests introduce ambiguity due to perceptual challenges such as multi-stability and difficulties associated with axonometric projections, which do not align naturally with human visual perception and can be complex to interpret
Bartlett & Camba (2022). Furthermore, 2D tests do not allow participants to move and explore the environment. This factor is crucial considering the role of proprioceptive feedback and the vestibular system in the encoding and maintenance of spatial configurations in memory. The lack of proprioceptive feedback means participants are unable to use the sensory information from their own movements and body positions to build and maintain accurate spatial representations. This omission neglects the dynamic and interactive nature of spatial learning and navigation, where proprioceptive cues significantly enhance the fidelity of the cognitive map by providing continuous updates about one's position and movement within the environment. (
Bayramova *et al*., 2021;
Fetsch *et al*., 2009;
Nardini *et al*., 2008). Here we define cognitive map as a mental representation of the spatial layout of an environment, allowing an individual to acquire, code, store, recall, and decode information about the relative locations of places, landmarks, and routes (
Tolman, 1948).

In our study, translational movement is not performed by participants. Instead, participants are seated in a swivel chair that allows them to actively rotate their torso left and right, enabling 360-degree exploration of the environment. These self-generated rotations provide limited but present vestibular and proprioceptive feedback. In particular, yaw-plane movements engage the vestibular system via stimulation of the semicircular canals responsible for detecting angular acceleration (
Ehtemam *et al.*, 2012), while proprioceptive input is involved through trunk muscle activity and postural adjustments during chair rotation (
Ivanenko *et al.*, 1999).

Moreover, vestibular signal processing during active rotation is known to depend on the match between predicted and actual proprioceptive feedback. When this match is present, the brain can suppress vestibular reafference, allowing for stable perception of self-motion. However, in the presence of a mismatch, vestibular neurons continue to encode the full signal, underscoring the functional role of proprioceptive input even in non-translational movement contexts (
Brooks & Cullen, 2014); (
Cullen & Zobeiri, 2021).

### Strategies of spatial orientation and navigation 

Large-scale spatial cognition involves complex processes such as learning spatial relationships between environmental objects, maintaining these relationships in memory, and using this knowledge to navigate and communicate spatial information (
Hegarty *et al.*, 2006). Vision is typically the primary sense for understanding spatial layouts, but non-visual senses also play critical roles, including the vestibular system, which informs about linear and angular accelerations (
Casale *et al.*, 2023), kinesthesis, which senses limb movement (
Ehinger *et al.*, 2014), and proprioceptive information about self-movement and body position originates from sensors in our muscles and joints (
Chance *et al.*, 1998;
Sheeran & Ahmed, 2020). Working memory helps piece together spaces from multiple perspectives, encoding information in various formats such as verbal sequences of route directions or spatial configurations (
Hegarty *et al.*, 2006). Research shows that encoding self-motion through body-based senses enhances the ability to create and use cognitive maps effectively (
Bayramova *et al.*, 2021). Two types of mental representation of spatial layouts are typically distinguished: Route Knowledge, which consists of rigid, egocentric representations based on sequential routes and landmarks (
Aguirre & D’Esposito, 1999), and Cognitive Maps, which are flexible, allocentric representations storing the identities and spatial relationships of landmarks (
Aguirre & D’Esposito, 1999;
Tolman, 1948). This strategy allows navigation using landmarks and their relative positions (
O’keefe & Nadel, 1979;
Tolman, 1948). Moreover, spatial navigation can rely on allocentric (approaches where an individual or organism navigates the environment using an external frame of reference, independent of their own position or orientation) and egocentric (approaches where an individual or organism navigates the environment based on their own position and orientation) strategies, and the distinction isn't always straightforward, often depending on individual differences, as well as task and environmental demands. The most reliable source of information dynamically determines the navigation approach, although disorientation can still occur in novel environments, highlighting the complexity of spatial navigation (
Fetsch *et al.*, 2009;
Nardini *et al.*, 2008). Environmental factors play a crucial role here; in landmark-rich environments, allocentric strategies tend to dominate, whereas featureless environments like deserts may rely more on egocentric cues, despite their potential for error and disorientation (
Souman *et al.*, 2009). Therefore, while allocentric and egocentric strategies provide foundational frameworks for understanding spatial cognition, navigation involves a complex interplay of these strategies and their integration with various cognitive processes. These factors must be considered in assessing spatial abilities

### Validation of a new 3D spatial task

In spatial cognition research, there is a notable gap concerning the development of programs designed to assess higher-level spatial abilities, such as the formation of cognitive maps in 3D environments.

Research has shown that individual differences in working memory and navigational strategies significantly impact the ability to form cognitive maps, with some individuals relying more on route-based navigation while others are better at forming place-based, map-like representations (
Weisberg & Newcombe, 2016).

Efforts to improve assessment performance, such as clarifying drawings, enhancing 3D appearance, or using physical models and animations, have shown positive results (
Cohen & Hegarty, 2012;
Fisher *et al*., 2018;
Yue, 2008). For instance, the "Spatial Configuration Task" (SCT,
Burles *et al.*, 2017) has been designed to investigate the generation of cognitive maps in a simple 3D Virtual Environment (VE). In this task, participants first become familiar with a space where objects are arranged for memorization. This task was designed to provide a quick and reliable measure of the ability to generate and utilize a mental representation of a simple virtual environment (VE), but it has never been implemented in an immersive virtual reality (VR) environment. 

However, these modifications have not yet been widely adopted in the evaluation of cognitive map formation abilities (
Bartlett & Camba, 2022). VR offers several advantages over traditional 2D and desktop 3D assessments of spatial abilities, including the ability to evaluate 3D maps in a fully immersive 3D environment. Additionally, VR can incorporate sensory information related to body movement, providing an additional source of input for cognitive map formation, thereby enabling a more ecological and realistic assessment. Therefore, we propose a protocol for validating a novel VR task, the Virtual Spatial Cognition Task (VSCT). This task simulates participants' cognitive map formation abilities by requiring them to explore a virtual environment, learn spatial relationships between landmarks, and recall their positions.

Developing a spatial task that allows users to explore the environment by rotating in a movable chair without the need for forward or backward movement not only leverages several benefits associated with gaze-directed steering (GDS) but also simplifies interaction by eliminating the need for complex movement controls, thus making VR more accessible, especially for users with limited mobility or dexterity.

 A significant advantage expected to feature this setup is represented by the reduced motion sickness. By restricting navigation to rotational exploration should avoid the sensory mismatch that often causes discomfort and enhances situational awareness, allowing users to freely observe their surroundings without the distraction of forward or backward movement.

Moreover, the design controls the visibility of virtual objects, requiring users to piece together information gradually, a feature shared also with the SCT.

This study aims to validate the newly developed VSCT by evaluating participants' performance on the original SCT both before and after VR exposure. We will use a
**between-subjects design**, dividing participants into two groups to clarify the specific effects of spatial versus non-spatial cognitive demands. One group will perform the task in virtual reality, while the other will engage in a non-spatial auditory verbal task, adapted from
Bacon *et al.* (2008), to isolate memory processes from spatial reasoning. To this end, only the first administration of the SCT (T1) will be used for correlation analyses with the VSCT, as it provides a baseline measure of spatial performance. The second administration (T2) is included solely for exploratory purposes—to investigate whether repeated exposure might lead to performance improvements and to preliminarily explore potential training effects. These exploratory findings could inform the design of future studies specifically aimed at assessing the impact of training or interventions. Establishing the VSCT’s validity is a necessary first step before we can confidently use it in such longitudinal or interventional contexts.

We will use a series of tests and tasks to validate the VSCT. We hypothesize a positive correlation between the VSCT and SCT, as both are designed to measure the same construct—namely, the ability to form cognitive maps. We also hypothesize a positive correlation between the VSCT and Backward Corsi, as working memory is a key component in the formation and maintenance of cognitive maps (
Epstein *et al.*, 2017). Conversely, we do not expect a significant correlation between the VSCT and RAVLT. We included the Rey Auditory Verbal Learning Test (RAVLT) in our study precisely to assess discriminant validity. The RAVLT measures verbal episodic memory, while the VSCT targets visuospatial configuration memory—two constructs that are theoretically and empirically distinct (
Suri *et al.*, 2017). By including the RAVLT and confirming that it does not significantly correlate with performance on the VSCT, we provide evidence that the VSCT is not simply capturing general memory ability, but rather a more specific visuospatial memory component. This lack of correlation supports the discriminant validity of our task, helping to confirm that it measures a construct different from that assessed by standard verbal memory tasks.

Finally, to evaluate VSCT feasibility we will use the Simulator Sickness Questionnaire (SSQ) (
Kennedy *et al*., 1993).

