### Participants

As the study aims to evaluate
**convergent and discriminant validity** of VSCT, by comparing VSCT correlation with SCT to the correlation of RAVLT with SCT, an
*a priori* power analysis was conducted using

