*Procedure*
**

 Participants will be assigned in a pseudo-randomized single-blinded manner to one of the two groups (Auditory Verbal (AV) vs. Virtual Reality (VR)). Both groups will be asked to perform an initial assessment of their spatial abilities using the 40-item version of SCT. In the next phase, the experimental group will be made to wear the "HTC VIVE" visor that will allow them to perform the Virtual Spatial Configuration Task in VR (VR condition); the control group will be administered the auditory verbal memory task (AV condition). Both groups will be given the SCT again at the end of the task (See
Figure 2). 

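### The hypothesised VSCT-RAVLT correlation cannot be computed because each task goes to a different group; only the indirect contrast through the SCT can be estimated

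*Protocol article*

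**What the plan says.** In the Introduction, under Validation of a new 3D spatial task, the protocol article states: "Conversely, we do not expect a significant correlation between the VSCT and RAVLT". It then treats that result as evidence: "By including the RAVLT and confirming that it does not significantly correlate with performance on the VSCT" is said to show that the VSCT measures something more specific than memory in general.

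The same section fixes a between-subjects design: "One group will perform the task in virtual reality, while the other will engage in a non-spatial auditory verbal task". The Procedure repeats this. The experimental group performs the VSCT, and "the control group will be administered the auditory verbal memory task (AV condition"). The AV memory task condition section identifies that task as the RAVLT. The SCT is common to both arms: all participants take it at the start, and "Both groups will be given the SCT again at the end of the task".

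The Participants section describes the validity aim differently, "by comparing VSCT correlation with SCT to the correlation of RAVLT with SCT", and adds that the two groups will be correlated with different variables.

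Two other places matter. The lead-in to the spatial tasks under Instruments refers to each participant and then lists the SCT and the RAVLT. The Correlation analysis section plans a matrix of Corsi, SBSOD, VSCT and SCT, without the RAVLT.

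**The concern.** A correlation needs both scores from the same people. The allocation in the Procedure never produces such a pair for the VSCT and the RAVLT, so the hypothesis can be neither supported nor refuted. This is a contradiction between a stated hypothesis and a stated procedure, and no analysis plan can repair it after data collection.

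What is at stake is the claim that the VSCT is not a general memory test. Some verbal coding is plausible, because the task uses nameable household objects and canvas questions with three answer choices (Scene setup; The virtual task). If the report claims discriminant validity in the Introduction's terms, no data will stand behind it.

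**Working it through.** **1. The plan's own sample size.** Inputs from Participants: q = 0.4, alpha 0.05, power 0.95, stated N = 166. Sidedness is not stated; two-sided is assumed. For two independent correlations in equal groups:

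n per group = 2 × ((1.960 + 1.645)/0.4)² + 3 = 165.4, so 166 per group and 332 in total.

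The figure 166 is therefore reproduced, but as a per-group number. If 166 is the total, split 83 and 83 (a 1:1 ratio is assumed), power for the cross-group contrast is Φ(0.4/√(2/80) − 1.960) = Φ(2.530 − 1.960) = 0.72. One-sided it is 0.81. This matters here only because the cross-group contrast is the one that can be computed.

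**2. Who has which score** (Instruments, Procedure, AV memory task condition):

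| Score | VR group | AV group |
|---|---|---|
| SBSOD, Backward Corsi | yes | yes |
| SCT, first administration (T1) | yes | yes |
| VSCT | yes | no |
| RAVLT | no | yes |
| SCT, second administration (T2) | yes | yes |

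r(VSCT,SCT T1) can be estimated in the VR group and r(RAVLT,SCT T1) in the AV group. The number of VSCT-RAVLT pairs is 0. The Introduction fixes T1 for correlations with the VSCT; using T1 for the RAVLT as well is an assumption made for comparability.

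**3. Does the computable contrast settle the missing correlation?** With a = r(VSCT,SCT) and b = r(RAVLT,SCT), a valid correlation matrix requires only that r(VSCT,RAVLT) lie within

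ab ± √((1 − a²)(1 − b²)).

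The documents give no values for a or b, so these are assumptions:

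| a | b | Lowest possible r(VSCT,RAVLT) | Highest possible |
|---|---|---|---|
| 0.50 | 0.10 | −0.81 | +0.91 |
| 0.50 | 0.15 | −0.78 | +0.93 |
| 0.60 | 0.28 | −0.60 | +0.94 |
| 0.38 | 0 | −0.92 | +0.92 |

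First row: 0.05 ± √(0.75 × 0.99) = 0.05 ± 0.862. The last three rows have a difference q close to the protocol's 0.4. In every row the range includes both zero and a very strong positive correlation.

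**4. Would non-significance suffice if pairs existed?** For an observed r of 0, the 95% confidence limits are ± tanh(1.96/√(n − 3)): about ±0.22 with n = 83 and ±0.15 with n = 166. A non-significant result would leave modest correlations open, so it would not confirm that there is none.

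**The case against.** Three arguments deserve weight.

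*The Instruments section can be read as giving the RAVLT to everyone.* Its lead-in does refer to each participant. But it introduces a list of instruments, while the design statement in the Introduction, the remark in Participants about two groups and two variables, and the Procedure all assign the RAVLT to the control group. The specific text prevails. The lead-in still conflicts with it and should be reconciled.

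*The discriminant aim survives.* A reader might infer from the missing pairs that one of the two validity aims cannot be answered at all. The documents do not support that. Participants frames the joint validity aim as a contrast of two correlations with the SCT, and both can be estimated. What fails is the Introduction's hypothesis and the claim drawn from it. Nor do the wide bounds show that the VSCT does load on verbal memory; they show only that the planned data could not exclude it. The shared Corsi and SBSOD scores might narrow the bounds but would not identify the correlation.

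*Giving everyone both tasks looks easy.* A reader might also infer that 166 participants would then be amply powered. With assumed correlations of 0.50 for VSCT-SCT and 0.15 for VSCT-RAVLT, and 0 to 0.15 for SCT-RAVLT, Steiger's test has about 94% to 97% power at N = 166. This does not support the protocol's sample size. The correlations are assumed, the contrast differs from the one in Participants, and 166 matches only the per-group number there. The redesign also costs more than one extra task. AV participants would need VR training and testing, and would meet the VSCT after two SCT administrations where the VR group has had one. Adjusting for group removes a mean shift, but not a practice effect on the correlation.

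**Conclusion.** The point holds in a limited form. Under the stated procedure the VSCT-RAVLT correlation has no paired observations, so the Introduction's hypothesis and the claim built on it cannot be tested. That follows from the text and rests on no numerical assumption beyond reading the Procedure as overriding the Instruments lead-in.

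The contrast in Participants remains available but answers a narrower question: whether verbal memory predicts the SCT less well than the VSCT does. Under the assumed values it leaves r(VSCT,RAVLT) almost unconstrained (−0.81 to +0.91 for 0.5 and 0.1). The convergent hypothesis, VSCT with SCT T1, is unaffected. The text needs correcting; a redesign is not required.

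**What to change.** Required, at the cost of wording and a weaker claim:

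- Delete the VSCT-RAVLT hypothesis from the Introduction, with the statement that its confirmation shows the VSCT is distinct from general memory.
- State r(VSCT,SCT T1) against r(RAVLT,SCT T1), compared across groups, as the discriminant analysis.
- Add the RAVLT-SCT correlation and this comparison to the Correlation analysis section.
- Reconcile the Instruments lead-in with the Procedure, so that it is clear who takes the RAVLT.
- Limit the conclusion to whether the RAVLT predicts the SCT less well than the VSCT does.

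Optional, if a direct answer is wanted: after SCT T2, have participants take the other group's task. T1, the allocated task and T2 stay as they are. Estimate r(VSCT,RAVLT) with a confidence interval, adjusted for group, and compare it with r(VSCT,SCT T1) by Steiger's test for dependent correlations. Do not read non-significance as proof of no correlation. The cost is a longer session, VR training and testing for the AV group, an ethics notification, and order and practice effects that group adjustment only partly removes. The sample size for this contrast would need its own justification.

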**G*Power 3.1**
Faul *et al.* (2009). Assuming a
**moderate to large effect size (Cohen’s q = 0.4)**, a significance level of
**α = 0.05**, and a desired power of
**0.95**, The required sample size for comparing two independent correlation coefficients using a z-test for dependent Pearson’s r was calculated as 166
**participants**. Taken this for granted, and bearing in mind that the data to correlate are not yielded with a paper-and-pencil questionnaire- but a virtual setting requiring training and adaptation, we weight the effect size indication with previous research using similar aims and methods.

This was the case in
da Costa *et al.* (2022), who validated two immersive virtual reality tasks for spatial orientation using correlational and group comparison analyses. The authors reported significant associations between the virtual tasks and traditional cognitive measures, as well as successful group discrimination.

The participants represented a sample size large enough to yield statistically reliable confidence intervals. It should be noted that the study employed a between-subjects design; however, participants from the two groups were combined. In contrast, our study will correlate the two groups with two different variables.

Furthermore,
*
He *et al.* (2022)
* employed a fully within-subjects design to validate a spatial perspective-taking task in ambulatory virtual reality, using a sample size comparable to ours. However, since within-subjects designs typically offer greater statistical power, we acknowledge that our between-subjects design may require a larger sample to achieve equivalent sensitivity. We have accounted for this by adopting a conservative effect size estimate and grounding our decision in the specific demands of VR-based testing, which introduces variability due to training and adaptation phases.

Participants will be actively recruited to participate in the intervention across various University of Bologna Campus locations. Recruitment will be facilitated through targeted advertisements and consecutive enrollment procedures to ensure diverse participant representation and data robustness. 

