### Materials

**
*Instruments*
**

Individuals who agree to participate will be assessed online through a link to the questionnaires (via Psytoolkit and Qualtrics platform). The first evaluation will be carried out using an ad-hoc form to collect sociodemographic data and the following psychometric tests. 

*Santa Barbara Sense of Direction Scale* (SBSOD): The SBSOD assesses a participant’s self-reported sense of direction. The scale consists of 15 orientation-related statements (e.g. ‘I am very good at giving directions’) that participants rate on a seven-point Likert scale ranging from Strongly Agree (1) to Strongly Disagree (7). The SBSOD significantly correlates with measures of large-scale spatial skills in numerous experiments (
Hegarty *et al*., 2002;
Ventura *et al*., 2013).

*Backward Corsi Task*: The Backward Corsi Task (
Isaacs & Vargha-Khadem, 1989;
Kessels *et al*., 2008) is a cognitive tool designed to evaluate visuospatial working memory and attention by requiring participants to replicate sequences of block taps in reverse order.

The spatial performance of each participant will be measured using the following tasks.

*Spatial Configuration Task* (SCT): The Spatial Configuration Task is a quick and reliable measure of one's ability to generate and use a mental representation of the spatial configuration of different objects in a 2D virtual environment. (
Burles *et al*., 2017)

*The Rey Auditory Verbal Learning Test* (RAVLT) The Rey Auditory Verbal Learning Test (RAVLT) is a widely used neuropsychological assessment that measures verbal memory and learning. In this test, participants are presented with a list of 15 words, which they must recall across multiple trials. After a delay, they are asked to recall the list again and later recognize the words from a larger list of distractor words. The test assesses various memory functions, including immediate recall, learning ability, delayed recall, and recognition memory, helping evaluate cognitive functions related to verbal learning and memory (
Peaker & Stewart, 1989).

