**Figure 2. f2:**
[figure not shown]
Figure depicting the timelie of the experimental procedure.

**
*VR spatial task condition*
**

 Training: The participants will be placed in our virtual environment and instructed to explore the space around them in each of the scenes. In each scene, the participant will see 3 objects at a time (two in front of him and one behind him).

Testing: After the training is completed, participants will be asked to start the testing phase. This phase will last until the task is completed, namely, when the participant accurately recalls the position of the objects after three consecutive correct trials. The objects are those learned during the training phase. The participants' accuracy and reaction time will be recorded.

**
*AV memory task condition*
**

Administration of the RAVLT will involve several steps:

The experimenter will read the first list (List A) of 15 unrelated words at a rate of about one word per second. It's crucial to present the words in the same order and with the same pronunciation for each participant. After presenting the list, the participant will be asked to repeat back as many words as they can remember, regardless of the order. After the participant recalled as many words as possible from List A, the process will be repeated for five immediate recall trials. After each trial, the number of words correctly recalled will be recorded. 

The experimenter will read a second list (List A) of 15 unrelated words (List B) to the participant and instruct them to recall as many words as possible from this list. This step is designed to interfere with the participant's ability to recall words from List A. Following the presentation of List B, the participant will be asked to recall the words from List A once again. This step assesses the individual's ability to retrieve information from memory after interference.

After a short delay in which the participant will have to do a scrambled image test (usually around 20–30 minutes), the participant will be asked to recall the words from List A once more without presenting the word list again. This step evaluates the individual's ability to retain information in memory over time.

The participant's performance will be scored based on the number of words correctly recalled or recognized during each test phase.

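### The VSCT and the RAVLT are given to different groups, so the VSCT–RAVLT correlation on which the Introduction rests discriminant validity cannot be computed

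*Protocol article*

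**What the plan says.** All references are to the protocol article.

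- **Introduction, Validation of a new 3D spatial task (hypotheses).** The VSCT is expected to correlate with the SCT and with Backward Corsi, but not with the RAVLT. On the last of these: "By including the RAVLT and confirming that it does not significantly correlate with performance on the VSCT, we provide evidence", and the sentence goes on to conclude that the VSCT captures something more specific than general memory.
- **Same section (design).** "One group will perform the task in virtual reality, while the other will engage in a non-spatial auditory verbal task".
- **Methods, Procedure.** "Participants will be assigned in a pseudo-randomized single-blinded manner to one of the two groups". The experimental group is to "perform the Virtual Spatial Configuration Task in VR (VR condition"), while "the control group will be administered the auditory verbal memory task (AV condition"). Both groups take the SCT before and after.
- **AV memory task condition.** "Administration of the RAVLT will involve several steps". The VR condition describes only VSCT training and testing.
- **Methods, Participants.** The validity aim is described as a comparison of the VSCT–SCT correlation with the RAVLT–SCT correlation. The section adds that "our study will correlate the two groups with two different variables".
- **Materials, Instruments.** "The spatial performance of each participant will be measured using the following tasks". The SCT and the RAVLT follow in the list.
- **Plan of analysis, Correlation analysis.** The planned matrix covers Corsi, SBSOD, VSCT and SCT. The RAVLT is not in it.

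**The concern.** A correlation needs both scores from the same person. The hypothesis calls for VSCT and RAVLT scores in pairs, and the allocation puts the two tests in separate groups. The article states both, and they are incompatible, so this is not a detail left to an analysis plan: no plan can compute a correlation from unpaired data.

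At stake is the statement that the VSCT is distinct from verbal memory, which is the reason the article gives for including the RAVLT. If the study runs as described, that statement will have no data behind it. Neither a larger sample nor modelling can supply the missing pairs after data collection.

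**Working it through.** **Step 1. Who has which score.** From the Procedure, the two condition descriptions and the online first evaluation in Materials:

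| Measure | VR group | AV group |
|---|---|---|
| Corsi, SBSOD | yes | yes |
| SCT, before and after | yes | yes |
| VSCT | yes | no |
| RAVLT | no | yes |

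Participants with both VSCT and RAVLT: 0. The pairs VSCT–SCT and VSCT–Corsi exist in the VR group, and RAVLT–SCT exists in the AV group.

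**Step 2. The plan's own figure.** The Participants section gives 166 for q = 0.4, α = 0.05 and power 0.95. For two independent correlations (Fisher z, two-sided):

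n per group = 2 × ((1.960 + 1.645) / 0.4)² + 3 = 165.43, rounded up to 166.

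The figure reproduces as a number per group (332 in total) for a comparison between separate groups. That agrees with the allocation in Step 1. Whether 166 is meant per group or in total is a separate question; the number of VSCT–RAVLT pairs is zero either way.

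**Step 3. Can the computable contrast stand in for the missing correlation?** Let a = r(VSCT,SCT) and b = r(RAVLT,SCT). A valid 3 × 3 correlation matrix only requires that r(VSCT,RAVLT) lie within

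ab ± √((1 − a²)(1 − b²)).

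The document gives no values for a and b, so these are assumptions chosen to match q = 0.4.

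- Main illustration, a = 0.50 and b = 0.15. Check: atanh(0.50) − atanh(0.15) = 0.549 − 0.151 = 0.398, about 0.40. Bounds: 0.075 ± √(0.75 × 0.9775) = 0.075 ± 0.856, that is **-0.78 to 0.93**.
- b = 0, a = 0.380: 0 ± √(1 − 0.144) = ±0.925.
- b = 0.30, a = 0.610: 0.183 ± √(0.628 × 0.91) = 0.183 ± 0.756, that is -0.57 to 0.94.

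The bounds treat a and b as known and as describing one common population. Sampling error would widen them. Across these inputs, finding exactly the planned effect leaves r(VSCT,RAVLT) almost unconstrained, and a VSCT strongly related to verbal memory remains possible.

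**The case against.** Three objections deserve weight.

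1. **Materials may give the RAVLT to everyone.** Read literally, its introductory sentence covers each participant and is followed by the SCT and the RAVLT, in which case VR-group pairs would exist. But the sentence speaks of spatial performance, which does not describe a verbal test, and it only introduces an instrument list. The Procedure, the condition descriptions and the Participants section are specific and point the other way, and the correlation matrix has no RAVLT. The specific text prevails. What stands is that the article contradicts itself here and must be reconciled.

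2. **Discriminant validity has another test.** This stands in part. A reader might infer that the study can say nothing on discriminant validity, or that half of its validity aim is lost. The document does not support that: the contrast under Participants is computable from the two groups and is the one used for sizing. Its meaning is narrower, however. It shows whether the SCT relates more strongly to the VSCT than to the RAVLT, not whether the VSCT is unrelated to the RAVLT.

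3. **The bounds rest on assumed correlations.** True, and they are labelled so. They illustrate why the contrast is no substitute. The main point, zero pairs, does not depend on them.

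**Conclusion.** The point holds as an internal contradiction between hypothesis and procedure. Under the procedure as written, 0 participants contribute to r(VSCT,RAVLT), and the Introduction's conclusion about general memory is unsupported. This rests on reading the Procedure as overriding the loose sentence in Materials. It does not depend on the allocation ratio or on how 166 is counted.

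The consequence is confined to that hypothesis and conclusion. The convergent correlations of the VSCT with the SCT and Corsi are unaffected, and the between-group contrast remains available with its limited interpretation. The plan should be changed before enrolment, because the missing pairs cannot be recovered afterwards.

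**What to change.** **Minimum (wording only).**
- Delete the VSCT–RAVLT hypothesis from the Introduction, together with the conclusion that the VSCT is separate from general memory.
- Restate discriminant validity as the contrast of r(VSCT,SCT) in the VR group with r(RAVLT,SCT) in the AV group, and say what that contrast does and does not show.
- Make the sentence in Materials agree with the Procedure.

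The cost is a narrower claim; nothing changes for participants.

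**Alternative, if a longer visit is acceptable.**
- Give the RAVLT to the VR group after its second SCT, so that the SCT–VSCT–SCT sequence and the exploratory group comparison stay as planned.
- Amend the VR condition, and add the RAVLT to the matrix under Correlation analysis.
- Report r(VSCT,RAVLT) with a 95% confidence interval, not only a significance test. At an observed correlation of 0 the half-width is tanh(1.96/√(n − 3)): about 0.22 with 83 pairs (166 in total, 1:1 allocation assumed) and about 0.15 with 166 pairs.

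The cost is a considerably longer session: five learning trials, an interference list and a delay of 20 to 30 minutes. The VR group's RAVLT scores would also follow headset exposure and two SCTs, so fatigue or simulator sickness could affect the correlation. That limitation should be stated.
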